### Randomization

Random numbers will be generated using Statistics Analysis System (SAS) 9.2 software according to the principle of randomization. In order to implement random hiding, the random sequence will be kept by a trial manager. Using the remote random concealment method, it is determined that the basic information of qualified research individuals will be transferred by phone to the person who keeps the random numbers, from which the treatment allocation plan for each patient is obtained. Randomization of groups will be done according to a pre-made random scheme.

### Blinding

Due to the special color problem of the TCM injection, we anticipate that it will be difficult to achieve double-blinding during study. However, in order to avoid bias during the process, the following specific measures are proposed: (1) the researchers strictly adhere to the principle of randomization; (2) the doctors who participate in evaluation of the outcome are non-researchers, to ensure that evaluation of the efficacy of the test is blind; and (3) blood tests, data analysis, and statisticians to be covered up until the final analysis is completed. They only obtained the case report from (CRF) form and related data for analysis and did not understand the patient and drug use.

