**Methods:**

This study will employ the randomized, blinded, prospective, single-center experiments approach. Briefly, a total of 160 eligible patients will be equally randomized into three treatment groups and placebo control groups. Patients will receive appropriate treatments every 24 h for seven days after enrollment and followed up for 28 days. The main evaluation indicators will be cell count, serum high-sensitivity C-reactive protein (hs-CRP) level, monocyte chemoattractant protein 1 (MCP-1), interleukin-6 (IL-6), interleukin-1β (IL-1β), interleukin-8 (IL-8), interleukin-18 (IL-18), interleukin-10 (IL-10), tumor necrosis factor (TNF)-α, oxidized low density lipoprotein (OX-LDL), angina grade, and Traditional Chinese Medicine (TCM) symptom changes scale. Secondary indicators to be evaluated will include B-type natriuretic peptide (BNP) levels, troponin (cTn), muscle enzyme isoenzyme (CK-MB), heart-type fatty acid binding protein (H-FABP), liver and renal functions, as well as blood coagulation. Close monitoring of adverse events during the trial will also be conducted.

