## Methods/design

### Study design and settings

The present study will be set up using randomly blinded and single-center experiments. We will recruit 160 patients who meet the eligibility criteria at the Guangdong Provincial Hospital of Traditional Chinese Medicine. Subsequently, the participants will be divided into four equal groups: three groups with treatment (treatment group A will receive conventional drugs plus astragalus injection treatment, group B will receive conventional drugs plus *Salvia miltiorrhiza* injection, and group C will receive conventional drugs plus *Salvia miltiorrhiza* and astragalus injections) and the control group will receive conventional drugs plus 0.9% NaCl injection. The study design is as illustrated in Fig. 1.

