## Outcome measures

### Primary outcome measures

Cell counts, serum detection by enzyme-linked immunosorbent assay, including serum hs-CRP level, MCP-1, IL-6, TNF-α, IL-1β, IL-8, IL-18, OX-LDL, IL-10, improvement of angina [19], and TCM symptom change scale [20] are outlined in Tables 1 and 2.

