## Ethical issues

### Ethics statement

In clinical trials, researchers will comply with the Helsinki Declaration and ethical principles. The investigator will fully respect the individuals’ choices and will not force the individual to participate in the trial. The individual has the right to voluntarily participate, provide, and sign a written ICF, and may withdraw at any time. During recruitment, each participant will be assigned a random number to ensure blind implementation during the trial. In addition, researchers must protect the privacy and confidentiality of the individual.

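### The trial is labelled blinded and placebo-controlled, but no masking of patients or treating staff is described, and two symptom-based scales are primary outcomes

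*Protocol article*

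**What the plan says.** **Labels.** The abstract's Methods paragraph states: "This study will employ the randomized, blinded, prospective, single-center experiments approach". It describes patients as "equally randomized into three treatment groups and placebo control groups". Study design and settings repeats the label: "The present study will be set up using randomly blinded and single-center experiments". The Ethics statement says that "each participant will be assigned a random number to ensure blind implementation during the trial".

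**Blinding section.** It opens by saying that, because of the injections' colour, "we anticipate that it will be difficult to achieve double-blinding during study". Three measures follow: adherence to randomization; outside outcome assessors ("the doctors who participate in evaluation of the outcome are non-researchers, to ensure that evaluation of the efficacy of the test is blind"); and masking of blood tests, data analysis and statisticians until the final analysis is finished.

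**Infusions.** Under Trial treatment methods, the herbal products are diluted in 250 mL of 5% glucose and the control is described with 5% glucose, with 0.9% NaCl replacing glucose for diabetic patients. Study design and settings gives the control as 0.9% NaCl without that condition. Neither section mentions colour matching or a covered bag or line. Every patient has a 60-minute drip once a day for seven days.

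**Outcomes.** Primary outcome measures lists cell counts, nine serum markers and "improvement of angina [19], and TCM symptom change scale [20". The Sample size section names hs-CRP as the main effect index and sizes the trial on it.

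**The concern.** The labels suggest more protection than the Blinding section provides. A random number allocates a patient to an arm but masks nobody, so the Ethics statement does not fill the gap.

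The gap matters for outcomes that start with the patient. Table 2 scores chest pain, chest tightness, shortness of breath, weakness and palpitations, mostly by how the patient experiences them. A masked doctor who records the answers of a patient who knows the treatment does not have a blind source. If patients given the herbal infusion expect to improve, both symptom outcomes can move towards the active arms without any pharmacological effect. Because both outcomes are listed as primary, such a shift could be reported as a primary benefit in a trial described as blinded and placebo-controlled.

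**Working it through.** No stated figure is in dispute, so there is none to reproduce. The check has three parts.

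**1. Who is masked**

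| Party | What the article describes |
|---|---|
| Outcome assessors | Masked: non-researcher doctors (Blinding) |
| Blood testing | Masked (Blinding) |
| Data analysis and statisticians | Masked until the final analysis is complete (Blinding) |
| Patients | No measure described |
| Staff preparing or giving infusions | No measure described |

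The Blinding section presents its list as the specific response to the colour problem. Nothing on that list is directed at the patient or the treating team.

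**2. How many primary outcomes are exposed**

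- Cell counts: 1.
- Serum markers: hs-CRP, MCP-1, IL-6, TNF-α, IL-1β, IL-8, IL-18, OX-LDL, IL-10, which makes 9.
- Symptom-based: angina improvement and the TCM scale, which makes 2.
- Total: 1 + 9 + 2 = 12, so 2 of 12 depend mainly on symptoms. The other 10 are laboratory measures, and blood testing is masked.

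**3. Illustration of size**

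Inputs from the article: 40 per arm enrolled and 30 per arm calculated (Sample size); two-sample *t*-test against control, two-sided at 0.05 (Statistical analysis).

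Input that is assumed because the article gives none: an expectation shift *d* of 0.2, 0.3 or 0.5 SD in a continuous symptom score, with no true treatment effect.

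Formula: noncentrality λ = *d* × √(*n*/2), degrees of freedom 2*n* − 2, and false-positive rate = P(T > c) + P(T < −c), where T is noncentral *t* and c is the two-sided 0.05 critical value.

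| *n* per arm | c | *d* | λ | False-positive rate |
|---|---|---|---|---|
| 40 | 1.991 | 0.2 | 0.2 × √20 = 0.894 | 0.143 |
| 40 | 1.991 | 0.3 | 0.3 × √20 = 1.342 | 0.263 |
| 40 | 1.991 | 0.5 | 0.5 × √20 = 2.236 | 0.598 |
| 30 | 2.002 | 0.2 | 0.2 × √15 = 0.775 | 0.119 |
| 30 | 2.002 | 0.3 | 0.3 × √15 = 1.162 | 0.208 |
| 30 | 2.002 | 0.5 | 0.5 × √15 = 1.936 | 0.478 |

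This gives about 14%, 26% or 60% at 40 per arm and 12%, 21% or 48% at 30, per comparison, against a nominal 5%. Because last values are to be carried forward for patients who drop out, the number analysed probably lies between 30 and 40.

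**The case against.** **The limit is disclosed.** The article never says double-blind. It gives the reason for the difficulty and names who is masked. A reader might infer that the blinded label is false. The text does not support that: the label is unqualified where it appears and qualified only in the Blinding section. Disclosure does not, however, protect a symptom score that is kept as primary.

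**Visibility is inferred.** A reader might conclude that all 120 patients in the herbal arms can be told apart by colour from the 40 controls. The article does not say which product is coloured, or whether the colour still shows after dilution in 250 mL, and it says difficult, not impossible. A fuller protocol may also describe how bags are handled. Probable recognition is as far as the text goes.

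**The main outcome is largely protected.** A reader might infer that the whole trial is open to expectation bias. hs-CRP sizes the trial and its assay is masked, so that does not follow. One indirect route remains: unmasked clinicians could vary background therapy, which is open-ended and includes classes that the Background section calls anti-inflammatory.

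**Patient report is partly inferred.** Table 1 is not shown, doctors evaluate outcomes, and some Table 2 grades refer to medication use or function. Even so, most Table 2 grades depend on what the patient feels.

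**The size is hypothetical.** Nothing in the article anchors a shift of 0.2 to 0.5 SD. Controls also receive a daily drip, which narrows the contrast in expectation, and comparisons between herbal arms are less exposed. The false-positive rates show sensitivity to bias and do not estimate it.

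**Conclusion.** The point holds for the labels and for the primary status of the two symptom scales. The article calls the trial blinded and the control a placebo, but describes no masking of patients or treating staff and no visual match for the control. Expectation could therefore bias active-versus-control comparisons on 2 of 12 primary outcomes. hs-CRP and the other masked assays are much less exposed.

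This rests on two inferences: that the colour remains noticeable enough for patients to recognise the infusion, and that the angina measure, like most of Table 2, depends on what patients feel. The illustrative rates additionally assume the size of the shift. Separately, the two descriptions of the control infusion conflict and must be reconciled, because what the control looks like bears directly on masking.

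**What to change.** Before unmasking:

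- Make hs-CRP primary and move angina improvement and the TCM scale to secondary, interpreted as outcomes not blinded to the patient. This costs no planned power, because the sample size already rests on hs-CRP.
- Describe the trial throughout as assessor-, laboratory- and analyst-blinded, and say who is not blinded. Correct the Ethics statement on random numbers to match.
- Drop 'placebo' unless the control is visually matched, and reconcile the two descriptions of the control infusion.
- Use opaque covers on bags and lines in all four arms for remaining patients, and report the date of the change.

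**Cost.** A protocol amendment and registry update, the covers themselves, and loss of primary status for the two scales. Trial status gives recruitment as under way since 1 June 2019, so covers introduced now would leave a mix of masked and unmasked patients, which is why the date must be reported.

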## Intervention

### Trial treatment methods

According to the principle of randomization, the group to be screened will be divided into four groups. The three groups of treatment are as follows: Group A, which receives conventional drug treatment plus astragalus injection treatment (size 20 mL/support, packaging 10/container), Group B, which will receive conventional medicine plus *Salvia miltiorrhiza* injection (specification 20 mL/support, packaging 10/container) and Group C, which will receive conventional medicine plus an injection of *Salvia miltiorrhiza* combined with astragalus. Both *Salvia Miltiorrhiza* and Astragalus injections will be prepared with 250 mL of 5% glucose. The control group receives an injection containing 250 mL conventional drug plus 5% glucose. For diabetic patients, an injection of 250 mL 5% glucose will be changed to 250 mL 0.9% NaCl. All patients will receive an intravenous drip once a day for 60 min for a treatment period of seven days.

The conventional drugs used in the stable coronary heart disease test will be as described in the ESC Guidelines for the diagnosis and treatment of SCAD [18]. The standard is given as aspirin, clopidogrel, low molecular weight heparin, statins, nitrates, beta-blockers, ACEIs, and other drugs.

### Pharmaceutical and combination methods

For allocation and combination of the drugs in this test, we will prepare *Salvia miltiorrhiza* injection and astragalus injection using 250 mL of 5% glucose. If the patient is diabetic, we will change 250 mL of 5% glucose injection into 250 mL of 0.9% NaCl. No other injections will be used simultaneously during intravenous infusion.

### Matters needing attention

During the study, patients will receive the test drug within 24 h of enrollment. Conventional treatment of stable coronary heart disease (such as anti-poly drug, lipid-lowering drug, antihypertensive drug) will be carried out at the same time. Injections of astragalus and *Salvia miltiorrhiza* should not be used as a substitute.

### Content and data capture points

The contents and key points of the data to be collected during the study include the screening period (one day), 24 h before recruitment, a treatment period of 1–7 days followed by daily recording of data, and follow-up on the 28th day after treatment.

## Outcome measures

### Primary outcome measures

Cell counts, serum detection by enzyme-linked immunosorbent assay, including serum hs-CRP level, MCP-1, IL-6, TNF-α, IL-1β, IL-8, IL-18, OX-LDL, IL-10, improvement of angina [19], and TCM symptom change scale [20] are outlined in Tables 1 and 2.

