### Sample size

This study will use a parallel design of randomized controlled trials and hs-CRP as the main effect index. Conventional Western medicine treatment can reduce hs-CRP by 32%, according to clinical conditions, and it is estimated that Chinese medicine can reduce hs-CRP by 52%. The set α = 0.025, β = 0.2, superiority limit value δ = 20%, and the sample size of each group will be calculated as 30 cases [16, 17]. Considering the loss of follow-up, 40 patients with stable coronary heart disease and 160 with four combinations will be selected.

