### Research process record points

The subject content and data at each time point, according to the patient’s hospitalization period, will be recorded as shown in Fig. 2. Specifically, the screening period (0 days) will be 24 h before recruitment followed by a daily data tracking and recording from day 1 to day 7, and a follow-up on day 28 after treatment is administered.

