### Statistical analysis

Statistical analysis will be performed using SPSS 19.0 statistical software. Measured data will be described using means and standard deviation of the mean, while count data will be by the number of cases in percentages. First, a baseline analysis of the demographic characteristics in the four groups of selected cases will be conducted to investigate the balance and comparability across groups. Then, the effectiveness and safety indices will be compared across the four groups. The comparison of iso-quantitative data between the experimental and the control group will be performed using a student *t*-test of two-sample comparison for group design, while the comparison of the two classification indicators such as gender will be performed using the Cochran-Mantel-Haenszel χ^2^ test or Fisher’s exact probability method. The missing supplementary data will be adjusted using imputation methods. To validate ineffectiveness among the groups, we will perform a rank sum test of the two-sample comparison in the groups. All statistical tests will be two-sided with *p* ≤ 0.05 to be used for statistical significance.

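### Twelve unranked primary outcomes, three active arms and an unadjusted two-sided 0.05 for every test do not hold the 5% level, although the trial is sized on hs-CRP alone

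*Protocol article*

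**What the plan says.** Under Primary outcome measures the article lists "Cell counts, serum detection by enzyme-linked immunosorbent assay, including serum hs-CRP level, MCP-1, IL-6, TNF-α, IL-1β, IL-8, IL-18, OX-LDL, IL-10, improvement of angina" and then the "TCM symptom change scale". That makes cell counts, nine serum markers, angina improvement and the TCM scale, twelve items in no order of priority. The Methods paragraph of the abstract gives the same twelve, beginning "The main evaluation indicators will be cell count, serum high-sensitivity C-reactive protein (hs-CRP) level", so the list is not a slip in one place.

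The Sample size section takes "hs-CRP as the main effect index" and bases the number of patients on that marker only.

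Under Study design and settings, "the participants will be divided into four equal groups": three active and one control. Under Statistical analysis, the comparison of quantitative data "between the experimental and the control group will be performed using a student" two-sample test. The same section ends with "All statistical tests will be two-sided with" p ≤ 0.05 as the threshold. No ranking of the twelve, division of alpha, co-primary rule or adjustment is stated.

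**The concern.** The article gives two answers to what the trial is about: one marker when it counts patients, twelve outcomes when it names what is primary. It then gives every test the full 5%. If that text is followed, any one of about 36 nominal results can be reported as an effect on a primary outcome. The reader cannot tell a real effect from the best of many chance results.

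This is not detail left to an analysis plan. The threshold for all tests is written down, and so is the list. A later plan that adjusted for multiplicity would depart from the Statistical analysis section, and one that made hs-CRP the only primary outcome would depart from the Primary outcome measures section.

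**Working it through.** **The plan's own figure.** The Sample size section gives 30 per group from hs-CRP reductions of 32% and 52%, α = 0.025 and β = 0.2. It states no SD, so 30 cannot be confirmed. With means, n = 2(z_α + z_β)²(SD/20)², and n = 30 implies an SD of about 27.6 percentage points if α is one-sided 0.025, or 25.1 if it is two-sided 0.025. The step to 40 fits a 25% loss: 30/(1 − 0.25) = 40. None of the error rates below depends on this. It matters only for the cost of the fix.

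**Number of tests.** Outcomes: 1 (cell counts, taken as one item) + 9 (serum markers) + 1 (angina) + 1 (TCM scale) = 12. Contrasts with control: 3, one per active arm. Tests: 12 × 3 = 36, at one time point.

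**Expected false positives** if no arm affects any outcome: 36 × 0.05 = 1.8, whatever the correlation. In favour of an active arm: 36 × 0.025 = 0.9.

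**Chance of at least one, independent tests.** Two-sided: 1 − 0.95^36 = 0.842. Favouring an active arm only: 1 − 0.975^36 = 0.598.

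**Chance of at least one, shared control and correlated outcomes.** The article gives no correlations, so a common correlation ρ among the twelve outcomes is assumed and varied. For arm k and outcome j the test statistic is Z = (X_kj − X_0j)/√2, with X standard normal and correlation ρ between outcomes within an arm. The proportion of simulated trials (200,000 or more for each ρ) with any |Z| > 1.96, or any Z > 1.96, is:

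| Assumed ρ | Any two-sided p ≤ 0.05 | Any result favouring an active arm |
|---|---|---|
| 0 | 80% | 54% |
| 0.3 | 73% | 42% |
| 0.5 | 63% | 33% |
| 0.7 | 49% | 25% |

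Repeat runs differ by up to about one percentage point. The two-sided figure falls below 50% at ρ of about 0.69, and the favourable-only figure at about 0.09.

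**hs-CRP as the only primary outcome.** Three contrasts with a shared control, each at two-sided 0.05, give about 12.6% (1 − 0.95³ = 14.3% if independent). In favour of an active arm it is about 6%, against a nominal 2.5%.

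**Power under the fix.** The standardised difference d is solved from a two-sample t-test with n = 30 and 80% power. It is 0.736 if the planned alpha is equivalent to two-sided 0.05, and 0.814 if it is two-sided 0.025. Power at Bonferroni α = 0.05/3 = 0.0167 (t-test with 2n − 2 degrees of freedom, non-centrality d√(n/2)) is then:

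| Evaluable per arm | d = 0.736 | d = 0.814 |
|---|---|---|
| 30 | 65% | 75% |
| 40 | 80% | 88% |

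**The case against.** The strongest reply is that the Sample size section already supplies the hierarchy. hs-CRP is on the primary list and is singled out as the main index, so the rest may be a badly labelled supporting set rather than a contradiction. That reading is fair. It brings the error rate down from the 49–84% range to about 12.6%, but not to 5%. Nor does the sample-size α of 0.025 help. Read as one-sided, it is simply two-sided 0.05 for one comparison, and the analysis section tests at 0.05 in any case.

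Second, 36 is partly inferred. The Statistical analysis section speaks of comparison across four groups and then of experimental against control. Three contrasts per outcome is the likely reading, but it is not spelled out.

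Third, a reader might infer that a false claim of success is more likely than not. The documents do not support that. They give no rule by which one significant item makes the trial positive, and no correlations. The two-sided figures also include results in which an active arm does worse. Counting only favourable results at one time point, the chance passes 50% only when the outcomes are almost uncorrelated.

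Fourth, a reader might multiply the 36 by the daily records on days 1 to 7 and "a follow-up on day 28 after treatment is administered". The text does not say that the serum markers are drawn at every visit. The schedule is in a figure that is not shown, and the full protocol may name a primary time point. No such multiplication is claimed here.

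**Conclusion.** The point stands. Followed as written, the article does not hold a 5% error rate for its primary outcomes. At one time point, with no effect of any arm on any outcome, the chance of at least one false-positive primary result is about 49% to 80% for correlations from 0.7 down to 0 with the shared control, and 84% under full independence. For results favouring an active arm it is about 25% to 54%, and 60% under full independence. On the reading kindest to the plan, with hs-CRP as the only primary outcome, it is still about 12.6% two-sided.

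These figures assume three contrasts per outcome, equal correlation among outcomes and approximately normal test statistics. The correlations are assumptions, so the ranges should be quoted rather than any single value. The conclusion concerns false-positive primary results, not the probability that the trial is declared a success, which the article does not define.

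**What to change.** Before unblinding:

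- Name hs-CRP at one pre-stated time point as the single primary outcome, in line with the Sample size section. Day 7, the end of treatment, is one example; the choice is the sponsor's.
- Move the other eleven outcomes to secondary, and report them with confidence intervals as supportive.
- Control the three active-versus-control contrasts at an overall two-sided 0.05, by Dunnett or Holm, or by a fixed sequence whose order the sponsor states in advance. The article gives no arm priority, so the order is not prescribed here.
- Amend the Statistical analysis section and the abstract to match.

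The cost is wording changes and some power per contrast. With Bonferroni, which Holm improves on, power is about 65% to 75% with 30 evaluable per arm. It reaches 80% to 88% only if all 40 per arm are evaluable, although the extra ten were added to cover loss to follow-up. Both ranges rest on an effect size solved back from n = 30, because no SD is given. A fixed sequence leaves the first contrast at the full 0.05 and costs it nothing, but each later contrast can be claimed only if the ones before it succeed. All markers can still be measured as planned.
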